## Abstract

**Background:**

The prevalence of obesity with aging is escalating alarmingly; and pelvic organ prolapse (POP) and stress urinary incontinence (SUI) are now becoming a growing epidemic among the elderly. Synthetic transvaginal mesh has been employed with increasing popularity in the treatment of POP and is usually highly effective in controlling the principal symptoms of prolapse. However, studies have reported that mesh operations provide fairly unfavorable SUI cure rates. Therefore, additional anti-incontinence surgical strategies are increasingly being scrutinized to achieve better postoperative continence without any significant side-effects for patients with both POP and SUI. We hypothesize that the modification with the fixing of the mesh to the mid-urethra is superior to the original transvaginal mesh operation (TVM) with regard to anti-incontinence.

**Methods:**

One hundred and thirty patients diagnosed with POP–Q II–III and concomitant SUI requiring surgical treatment will be included in this prospective, randomized, double-blind, controlled clinical trial. Patients will be randomly allocated to receive either original TVM (TVM group, *n* = 65) or modified TVM surgery (mTVM group, *n* = 65). As the primary outcome parameter, we will evaluate the objective SUI and POP cure rates. Secondary endpoints include postoperative morbidity as assessed with the International Urogynaecological Association classification and subjective prolapse and incontinence cure rates reported by questionnaires.

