#### Sample size calculation

As we have newly developed the modification to the prosthesis surgery, an exploratory pilot study was designed to evaluate the feasibility of the modification to the mesh for the treatment of SUI. Twenty patients with SUI and POP were recruited for a mTVM operation by the same two senior surgeons who are conducting this randomization study. The sample size calculation study was designed based on preliminary data on the 20 patients. The newly developed technique yielded an objective SUI cure rate of 92% as opposed to 72% for the original TVM published by Sergent et al. [13, 17]. Sample size calculations were performed with G*Power software [29], using the statistical model for an χ^2^ approach. Consequently, sample size was estimated theoretically and an effect size of = 0.1, indicating a small effect, will be accepted. The sample size was calculated for the primary outcome of the SUI cure rate with the following assumptions: α = 0.05, power (1–β error probability) = 0.8, number of groups = 2. Based on these assumptions, a total sample size of *N* = 130 was estimated. In anticipation of dropouts (10%: *n* = 16) or a violation of protocol (10%: *n* = 16), a final sample size of *N* = 162 (81 participants per group) results.

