### Statistical analyses

Analysis of the patients will follow the CONSORT flow diagram (Fig. 1) through the phases of the study (enrollment [assessed, excluded, randomized], allocation [control group and experimental group with intervention received or not received], follow-up [lost to follow-up, discontinued intervention] and analysis) [30].

All statistical analyses will be conducted using SPSS software version 22 (IBM, Armonk, NY, USA). All tests will be two-sided and significance will be set at *P* < 0.05. Efficacy measurements were adjusted by intention-to-treat analysis. Missing values will be replaced using the last observation carried forward (LOCF) method. No subgroup analyses are planned. Standard deviations, 95% confidence intervals, and median will be used for the descriptive analyses. Primary and secondary outcome analysis: the Chi-square test or Fisher’s exact test will be employed to identify any objective outcome differences among groups.

Generally, continuous data will be checked for normality using the Shapiro–Wilk test. If the normality assumption is violated, then PISQ-12 and PFDI scores as tertiary outcomes will be normalized by log transformation (log10(x)). Univariate-repeated measure analysis of variance (ANOVA) will be used to determine the secondary outcome between and within the two groups (mTVM, TVM group) at six endpoints (before intervention and during follow-up clinical appointments 1–5 following intervention). Mixed design ANOVA will be carried out to determine the effects of the modified operation on subjective cure rate for POP and SUI, and the Bonferroni post hoc test will be used to test the difference between means. All statistical analyses will be completed after the final measurement of the last patient during the last clinical appointment after intervention. The repeated measure design with seven points in time allows us to monitor how patients change over time in both short-term (before/during intervention) and long-term situations (before/after intervention).

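### The abstract randomises 130 women (65 per group) but the sample size section ends at 162 (81 per group), so the article carries two recruitment targets 32 women apart

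*Protocol article*

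**What the plan says.** Abstract, Methods: "One hundred and thirty patients diagnosed with POP–Q II–III and concomitant SUI requiring surgical treatment will be included". The allocation is then given by group: "Patients will be randomly allocated to receive either original TVM (TVM group, *n* = 65) or modified TVM surgery (mTVM group, *n* = 65").

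Statistical methods, Sample size calculation: from cure rates of 92% and 72%, α = 0.05 and power 0.8, "a total sample size of *N* = 130 was estimated". The allowances follow: "In anticipation of dropouts (10%: *n* = 16) or a violation of protocol (10%: *n* = 16"), and with them "a final sample size of *N* = 162 (81 participants per group) results".

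Statistical analyses: "Efficacy measurements were adjusted by intention-to-treat analysis". The same section replaces missing values by last observation carried forward (LOCF), makes all tests two-sided, and names the chi-square test or Fisher's exact test for the objective outcomes.

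**The concern.** The abstract presents 130 as the number randomised. The sample size section uses the same figure as the requirement before losses and arrives at 162. This is more than condensation, because the abstract gives explicit group sizes (65 and 65) that conflict with the group sizes in the body (81 and 81).

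The target sample size decides when recruitment ends, and readers will check the final report against it. With two published targets, stopping at either 130 or 162 could be described as planned. If recruitment stops at 130, the allowance for losses has not been used, and the stated 80% power may not be met.

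**Working it through.** **Inputs.** Cure rates 92% (modified) and 72% (original), α = 0.05, power 0.8, required N = 130, two allowances of 10% (16 women each), final N = 162: Sample size calculation. Two-sided tests, chi-square or Fisher's exact, intention-to-treat, LOCF: Statistical analyses. Allocation 1:1: Concealment of group allocation. Abstract target: 130, 65 per group.

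**1. The plan's own figures.**
- Losses: 130 + 16 + 16 = 162. Equivalently 130 / (1 − 0.20) = 162.5. The derivation of 162 is sound, and it uses 130 as the number before losses.
- Required N: for 92% versus 72%, two-sided Fisher's exact power first reaches 80% at 64 per group (79.8% at 63, 80.6% at 64), a total of 128. At 65 per group it is 81.4%. So 130 is close to a Fisher calculation. The uncorrected chi-square formula gives 57 per group, a total of 114.

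**2. Gap between the targets.** 162 − 130 = 32 women, 16 per group.

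**3. Numbers left for analysis.**
- 130 randomised, both allowances lost: 130 × 0.80 = 104 (52 per group), which is 26 below the plan's requirement of 130.
- 130 randomised, dropouts only lost: 130 × 0.90 = 117 (taken as 58 per group).
- 130 randomised, all analysed: 130 (65 per group).
- 162 randomised, both allowances lost: 162 × 0.80 = 129.6, about 130.
- 162 randomised, dropouts only lost: 162 × 0.90 = 145.8, about 146.

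**4. Power for 92% versus 72%, two-sided α = 0.05.** Three methods:
- Noncentral chi-square, 1 degree of freedom, noncentrality N·w². Here w = (0.20 / 2) / √(0.82 × 0.18) = 0.260, so w² = 0.0678. At N = 104 the noncentrality is 7.05, at 116 it is 7.86, and at 130 it is 8.81.
- Exact power of the uncorrected chi-square test: the binomial probabilities of all pairs of outcomes that the test rejects, summed.
- Exact power of Fisher's test: the same sum with Fisher's p ≤ 0.05.

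| Analysed (per group) | Fisher's exact | Noncentral chi-square | Exact chi-square |
|---|---|---|---|
| 104 (52) | 70.3% | 75.6% | 78.2% |
| about 117 (58) | 75.4% | 80.1% | 83.3% |
| 130 (65) | 81.4% | 84.3% | 86.5% |

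The first row is below 80% by every method. The second row falls short by Fisher's test only. The third row meets 80% by every method. These figures take outcomes as observed and make no allowance for dilution by protocol violators or for error in carried-forward values.

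**The case against.** The strongest reply is that the power loss is conditional. The written analysis is intention-to-treat with LOCF, which keeps all randomised women. With 130 randomised and all analysed, nominal power is 81% to 87%. With dropouts alone lost, the chi-square model that the sample size section names still gives 80% or more. Even at 104, the exact chi-square miss is 1.8 points. This stands: a reader might infer that a target of 130 certainly misses the planned power, and the article does not support that. The reply does not remove the problem, because the sample size section treats the 20% as a reduction to be made good, and on that basis 130 randomised is too few.

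A reader might also infer that the plan contradicts its own intention-to-treat rule by inflating for protocol violators. The sample size section never says that violators are excluded, and a margin for dilution is compatible with intention-to-treat. What is missing is a statement of what the second 10% is for.

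Nor is there an arithmetic error, since 130 + 16 + 16 is 162. It can fairly be said that the body calls 162 final and that the abstract merely carries the uninflated number. That is the likeliest explanation, but the readable text does not say so, and the flow diagram is not available to settle it.

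**Conclusion.** The point holds as an inconsistency between abstract and body: two recruitment targets, 130 and 162, differing by 32 women. This needs no calculation and rests on no assumption.

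The consequence for power is conditional. It is a clear shortfall (70% to 78%) only if recruitment stops at 130 and both allowances leave the analysis. It depends on the test (75% to 83%) if only dropouts leave, and it disappears nominally (81% to 87%) if all 130 are analysed. All these figures assume cure rates of 72% and 92%.

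The stated effect size of 0.1 does not match those rates, which correspond to w = 0.26. That is a separate issue and is not used here to favour either target.

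**What to change.** State one target throughout: 162 randomised, 81 per group. Correct the abstract, and label 130 as the number required before the loss allowances.

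Add one sentence saying that protocol violators stay in their allocated group in the intention-to-treat analysis, so that the second 10% is a margin. About 146 observed outcomes are then expected from 162, and 130 should not be described as the expected number observed.

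If 130 randomised is the real target, remove the final figure of 162 and restate the power for the number expected to be analysed: about 117 with dropouts only, about 104 if violators are also excluded.

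The first course changes wording only, since the plan already derives 162. If recruitment has in practice been run to 130, it also means recruiting 32 more women.

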**Discussion:**

Recognizing the importance of an additional surgical procedure for anti-incontinence management, we aim to investigate whether a stabilizing suturing of the mesh to the mid-urethra delivers superior SUI correction compared to the original prosthesis surgery.

**Trial registration:**

ClinicalTrials.gov, NCT02935803. Registered on 20 May 2016.

**Electronic supplementary material:**

The online version of this article (doi:10.1186/s13063-017-2314-8) contains supplementary material, which is available to authorized users.

## Background

Demand for pelvic organ prolapse (POP) and stress urinary incontinence (SUI) surgery is expected to increase due to an expanding rate of obesity among elderly women. POP is defined as the protrusion of the pelvic organs from the normal anatomical location toward or through the vaginal opening; the current prevalence of symptomatic POP is in the range of 3–8% [1, 2]. SUI, classified as involuntary loss of urine during physical activities and a resultant increase in intra-abdominal pressure, is also highly prevalent, reaching as high as 24.8% [3].

Also of note, one-fifth of women in the United States receives surgery either for SUI or for POP [4], where the cumulative risk for SUI surgery is 13.6% and that for POP surgery is 12.6% [4]. Both pathologic conditions develop in > 50% of the women affected [5]. Synthetic transvaginal mesh (TVM) has been increasingly employed in the treatment of POP and tension-free slings are useful in the management of incontinence. Synthetic mesh during repair has principally been used due to higher efficacy compared to that of native tissue repair and resorbable mesh; however, complications appear to be more prevalent [6–9]. Common complications include mesh extrusion, chronic pelvic pain, dyspareunia, and infection [7–10]. The anti-SUI efficacy of the prosthetic placement is barely 72–83% [11–13]; however, it is assumed that a combination of a synthetic mesh with the sling operation [5, 14–16] will substantially increase the cure rate for concomitant SUI.

Despite the increased consideration of the combined surgery for both genitourinary pathologies in one session, there is a lack of consensus on the optimal treatment. It is supposed that a combined operation with mesh and sling is highly effective for the treatment of POP and SUI; however, the complication rate is elevated [5, 14–16].

Therefore, the research group developed a modification to the transobturator four-arm TVM [13, 17] to increase its anti-incontinence effect. While the sling is located beneath the mid-urethra, the TVM elevates the distal part of the anterior vaginal wall [13, 17]. In the original TVM, the posterior part of the mesh is anchored to the anterior aspect of the cervix and the anterior arms are spread under the bladder neck with stabilizing sutures. We hypothesize that the original TVM operation can be followed by residual SUI since the strengthening of the back arms may result in a backward dislocation of the entire mesh. The posterior movement of the mesh allows the dorsal rotation of the urethra since the mid-urethra is not suspended. The proposed modification to the original surgical procedure includes the suture of the anterior part of the mesh to the mid-urethra to prevent the mesh sliding. We think that the appropriate elevation of the mid-urethra would thus occur with the anterior arms and that would achieve a more effective anti-incontinence. The pubourethral ligament is usually loose in SUI, but the anchored mesh would theoretically normalize its function and stabilize the urethra. Intra- and postoperative complication rates would be expected to be similar to those with the original four-arm TVM, but the modified TVM with the anchoring suture would be slightly superior with respect to POP repair and remarkably more effective in SUI correction. In our preliminary study, the anterior fixing of the TVM to the mid*-*urethra demonstrates as high an efficacy of anti-incontinence as 96.8% and an enormously reduced recurrence prolapse rate of 3.2% in (unpublished data). The mesh extrusion rate is particularly low and this may be due to the fact that the stabilizing sutures exert a lack of “folding/wrinkling” of the edge of the mesh, preventing a lifting up of the mesh which does not compress the mucosa and derange the periprosthetic vasculature.

A further modification to the TVM surgery is that the positioning of the mesh will occur 1.5 cm below the urethral meatus, leading to an elevation of the entire anterior vaginal wall including the anterior and middle compartments as well. By contrast, the original TVM surgery does not prevent anterior compartment prolapse [13, 17].

## Methods/design

### Study design

The present study is a single-center, prospective, double-blind (participant, investigator/surgeon, outcome assessor), randomized, controlled trial. The study will be conducted in accordance with the Declaration of Helsinki and has been approved by the local medical ethics committee at the University of Szeged under reference number 55/2016. The trial is registered under NCT 02935803, and patient recruitment started on 22 August 2016. The trial flow diagram is presented in Fig. 1 (CONSORT study flow diagram). The protocol follows the Standard Protocol Items: Recommendations for Interventional Trials (SPIRIT) checklist (see Additional file 1).

**Fig. 1 Fig1:**
[figure not shown]
CONSORT study flow *diagram*

#### Patient recruitment and consent procedure

Patients will be recruited from the urogynecology consultation at the Division of Urogynaecology, Department of Obstetrics and Gynaecology, University of Szeged, Hungary. All study participants will be provided an information sheet and a consent form describing the study in brief so they can decide whether to participate in the study. Each participant will be explicitly informed that participation in the study is voluntary, that she may withdraw from the study at any time and that withdrawal of consent will not affect her subsequent medical assistance and treatment.

##### Consent to publish

Written informed consent was obtained from the patients for publication of their individual details and accompanying images in this manuscript. The consent form is held by the authors in the patients’ clinical notes and is available for review by the Editor-in-Chief.

#### Participants considered for trial

This will be a prospective longitudinal study involving all patients successively scheduled for operation for symptomatic prolapse POP–Q grade II or III and coexisting SUI, who will be included in the study after informed consent has been obtained. Patients will be recruited in the Department of Obstetrics and Gynaecology at the University of Szeged. The study will be conducted for an estimated maximum of 18 months (between August 2016 and December 2017). Table 1 provides an overview of the patient recruitment and evaluation plan.

**Table 1 Tab1:** Schedule of assessments/data collection

Assessment	Recruitment before intervention phase	Intervention (surgery)	Follow-up				
			6 weeks	6 months	1 years	2 years	3 years
Assessment of eligibility criteria	x						
Written informed consent	x						
Gynecological examination: incontinence symptoms	x	x	x	x	x	x	x
Gynecological examination: prolapse	x	x	x	x	x	x	x
Urodynamic examination	x				x		x
Adverse events		x	x	x	x	x	x
Questionnaires: PISQ-12 and PFDI	x		x	x	x	x	x
Introital sonography	x				x		x
Urine culture	x			x	x	x	x

The symptomatic POP–Q Stage II–III (determined by the gynecological examination using the International Continence Society quantification system) [18] anterior vaginal wall prolapse is defined as the maximum extent of the prolapsed anterior and middle compartments being within 1 cm above and 6 cm below the hymen [19, 20]. According to the international POP guidelines (the EBU and NICE guidelines) [21, 22], if the condition disrupts the patient’s life and non-surgical treatment options have not helped, it should be treated surgically.

In all cases, SUI will be visualized after a complete physical examination is performed (verified by pad test/Bonney test/two-dimensional [2D] introital sonography and urodynamic examination). The severity of SUI was assessed using the Ingelman–Sundberg classification [23]. Urodynamic examinations comprising uroflowmetry, cystometrography, the pressure-flow study, and the abdominal leak point pressure test will be performed before surgery to objectively determine the coexisting symptomatic SUI based on the international guidelines (the EBU and NICE guidelines) [21, 22]. The abdominal leak point pressure test will be used as a standardized examination method for the evaluation of SUI with urine leakage as a sign. If the intra-abdominal pressure recorded at the point of urine leakage was < 40 cmH_2_O, the origin of the SUI was set as intrinsic sphincter deficiency (ISD) [24]. In the case of ISD, preoperative pelvic floor training (PFMT) will be recommended. If the patient is unwilling to participate in PFMT or if the training was unsuccessful, we will recommend mesh surgery. This will also be the case for suspected urethral hypermobility, i.e. if the intra-abdominal pressure at the point of urine leakage was > 60 cmH2O.

#### Introital ultrasound findings

In all cases, introital ultrasound (GE Voluson 730) will be performed with a standardized bladder-filling volume of 300 mL. The vaginal probe (5–9 MHz) will be placed in the area of the vaginal introitus at the level of the external urethral orifice, with the patient in a semi-sitting position. Ultrasound assessment of the bladder and urethra starts in the mid-sagittal plane.

During the sonography, we measure the longitudinal (L) distance between the bladder neck and the line through the lower edge of the pubic symphysis and the horizontal (H) distance between the bladder neck and the upper edge of the symphysis. The two distances are measured at rest (L1, H1), during contraction (L2, H2), on pressing or while coughing (L3, H3). Changes in these parameters during contraction of the levator muscle and on pressing serve to evaluate the reactivity of the pelvic floor muscles and the adequacy of the supportive structures of the urogenital organs [25]. The funneling of the proximal urethra during coughing as a typical stress urinary sign also will be examined [25].

### Inclusion and exclusion criteria

#### Inclusion criteria

Female adults aged > 40 years with coexisting pelvic floor defects will be recruited, at least one year following delivery, irrespective of parity and pre- or postmenopausal state, medically and physically fit for the measurement and therapeutic surgeries, and, in the case of systemic or local estrogen treatment, stable for the past three months before inclusion.

#### Exclusion criteria

Exclusion criteria are: urge, mixed incontinence or occult SUI; prolapse < grade II or > grade III POP–Q ([21, 22], https://uroweb.org/guideline/urinary-incontinence), apical or posterior compartment prolapse, dysuria (bladder tumor, neurogenic urinary bladder damage), a history of mesh use or anti-incontinence pelvic procedures; pregnancy (urine test to accomplish); lactation period not yet finished; current urinary tract or vaginal infection, menstruation on the day of examination; contraindications for measurements or interventions, for example, acute inflammatory or infectious disease, tumor or fracture; de novo systemic or local estrogen treatment (< 3 months); de novo drug treatment with anticholinergics or other bladder active substances (tricyclic antidepressants and selective serotonin reuptake inhibitors) and cancer of the pelvic organs.

#### Concealment of group allocation from participants

After the screening phase, patients will be randomly assigned to one of the two therapy groups (the TVM group or modified TVM (mTVM) group). The allocation sequence will be generated by the independent urogynecology secretariat using online randomization software (http://randomization.com); allocation ratio = 1:1 (TVM group:mTVM group). The allocation will be concealed in sealed, opaque, sequentially numbered envelopes, which will be stored at the operating theatre. All the women recruited will be numbered consecutively corresponding to the numbered envelopes. The envelope will not be opened until the general narcosis of the study participant has been established. To increase the validity of the trial, the assigned procedure will be blinded for the study participants throughout the follow-up period. The participants will be informed of allocated treatment after completing the study forms 12 months after the procedures. If major complications occur, the study participants and the outcome assessor will be also informed of the allocated treatment at the time of any suspected complication(s).

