### Randomization

The patients will be randomized to one of the study groups using a computer-generated list. Allocation concealment will be ensured by enclosing assignments in sealed, opaque, sequentially numbered envelopes, which will only be opened when the general narcosis of the study patient has been established [26].

Postoperative outcomes and sequalae will be assessed by an outcome assessor who is a gynecologist in a subspecialization program in urogynecology and also well trained in the transvaginal mesh operation. The outcome assessor will remain blinded to the type of intervention throughout the study.

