#### Blinding

Participants will be blinded against the type of TVM surgery received (original TVM vs mTVM). The participant information document will not provide any information on the differences in surgical protocols such that the women could ascertain their group allocation. All investigators involved in data acquisition, data analyses, and statistics will also be blinded against group allocation. The surgeons in charge of the therapy cannot be blinded against group allocation and therefore will not be involved in data acquisition, data reduction, data analyses, or statistics.

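### Participants are told their arm at 12 months of a 3-year follow-up, and the outcome assessor is told after a major complication, although the plan says both stay blinded throughout

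*Protocol article*

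**What the plan says.** All references are to the protocol article.

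- **Participants.** The section on concealment of group allocation says that "the assigned procedure will be blinded for the study participants throughout the follow-up period". The next sentence reads: "The participants will be informed of allocated treatment after completing the study forms 12 months after the procedures".
- **Outcome assessor.** The same section continues, after the condition "If major complications occur", that "the study participants and the outcome assessor will be also informed of the allocated treatment at the time of any suspected complication(s". The Randomization section says: "The outcome assessor will remain blinded to the type of intervention throughout the study". The Blinding section adds, with no exception: "All investigators involved in data acquisition, data analyses, and statistics will also be blinded against group allocation". The Measurement outcomes section also describes a blinded, non-operating examiner for visits up to 3 years.
- **Surgeon.** The Study design section calls the trial "double-blind (participant, investigator/surgeon, outcome assessor". The Blinding section says: "The surgeons in charge of the therapy cannot be blinded against group allocation", and keeps surgeons out of data collection and analysis.

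**The concern.** A blinded trial should say until when each party is blinded, and its procedures should deliver that. Here the operating rules end the blinding of participants, and in some women that of the assessor, before outcome collection ends.

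Two kinds of data are exposed. The first is self-report. PISQ-12 and PFDI scores define subjective cure of prolapse and incontinence, and a woman who knows which operation she had may answer differently. The sealed-envelope procedure in the section on secondary and tertiary endpoints keeps the assessor away from the questionnaire. It does nothing about what the woman herself knows.

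The second is assessment after a complication. The assessor is told the arm only for women who have had a particular kind of outcome. If such complications are more frequent in one arm, the share of unblinded assessments will differ between arms too. The cough test, the POP-Q measurement and the grading of complications all involve an examiner's judgement.

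**Working it through.** No sample size or power figure enters this point. The check sets the blinding statements against the visit schedule.

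**Step 1: participants.** Input: the follow-up columns of Table 1 and the 12-month disclosure rule.

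| Visit | PISQ-12/PFDI | Examination | Urodynamics and introital sonography | Participant under the stated rule |
|---|---|---|---|---|
| 6 weeks | yes | yes | no | blinded |
| 6 months | yes | yes | no | blinded |
| 1 year | yes | yes | yes | blinded when completing the forms |
| 2 years | yes | yes | no | knows her arm |
| 3 years | yes | yes | yes | knows her arm |

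- Questionnaire rounds after disclosure: 2 of 5, or 40%.
- Follow-up time after disclosure: 36 − 12 = 24 months; 24/36 = two thirds.
- Postoperative urodynamic and sonographic examinations after disclosure: 1 of 2 (3 years).

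The follow-up period cannot be read as ending at 12 months, because both Table 1 and the Measurement outcomes section extend it to 3 years.

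**Step 2: assessor.** The sentence on complications opens with major ones and ends with any that is suspected, so it allows two triggers.

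- Narrow reading: the assessor is told only when a major complication occurs.
- Broad reading: the assessor is told on any suspicion.

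Under either reading, the assessor knows the arm of some women before their follow-up ends. That contradicts the Randomization section, and also the Blinding and Measurement outcomes sections, none of which makes an exception.

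**Step 3: which analyses receive these data.** The Statistical analyses section puts all analysis after the last patient's last visit, so data collected after disclosure are included.

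- Questionnaires: the repeated-measures and mixed-design ANOVAs cover baseline and the five follow-up appointments. Two of those six time points are open-label, and no rule separates them from the rest.
- Objective outcomes: these are compared by chi-square or Fisher's exact test, so the mixing of blinded and unblinded visits in one model concerns mainly the questionnaires. However, the Primary endpoints section fixes no single time point, so examinations after 12 months may enter the primary comparison.

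**Step 4: surgeon.** Study design lists the surgeon as blinded; Blinding says this is impossible. The Blinding section gives the workable rule, so this is a labelling error with no bias of its own.

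**The case against.** The best counter-case accepts the wording conflicts and disputes the consequences.

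- *The primary endpoints are examiner-measured, and PISQ-12/PFDI rank lower.* This stands. Telling a woman her arm does not by itself unblind the assessor, although she may reveal it. Urodynamic readings are less exposed than self-report. A reader might infer that the 12-month disclosure undermines the primary comparison as a whole; the document does not support that.
- *Bias is not shown.* This stands. The document gives no complication rate and no direction or size of effect. The participant information withholds the differences between the procedures, and the article does not say how the arm will be described at disclosure. A reader might infer that women told they had the original operation will report worse results, but that is conjecture.
- *First detection of a complication precedes disclosure.* This stands. Only later grading and examinations in those women are exposed, and their number is unknown and may be small.
- *Telling the assessor may have a reason.* It may. A reader might infer that it serves no purpose because the surgeon already knows the arm. The document does not say who manages complications, so that inference is unsupported.
- *A reader might take every suspected complication, however minor, as a trigger.* The opening condition about major complications makes that uncertain.

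None of this removes the contradictions or makes the 2- and 3-year questionnaires blinded.

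**Conclusion.** The concern holds in this form. Followed as written, the plan does not deliver the blinding it claims. Two of five postoperative questionnaire rounds, covering the last 24 of 36 months, are open-label for participants. In women with a major complication, the assessor may know the arm from that point on, so unblinding depends on an outcome.

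The supportable statement is that this can bias the later self-reported outcomes, and the later examinations and complication grading in those women. How much, and in whose favour, cannot be derived. Visits up to 12 months in women without a major complication are unaffected.

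The conclusion assumes that Table 1 is the operative schedule and that the assessor who is told the arm continues to assess that woman, since no replacement is described.

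**What to change.** 1. Reconcile the sections on study design, concealment, randomization, blinding and measurement outcomes. State until when each party is blinded, and make the complication trigger unambiguous.
2. For participants, choose one of two routes. Either defer routine disclosure until the 3-year forms are complete, or keep disclosure at 12 months, make 12 months the last blinded patient-reported comparison and label the 2- and 3-year PISQ-12/PFDI results open-label.
3. Leave any disclosure needed for care untouched, but withhold the allocation from whoever carries out that woman's later outcome assessments. Where this is not possible, log the unblinding with its date, flag the assessments made after it, and add a sensitivity analysis that treats them separately.
4. Describe the trial in Study design as participant- and assessor-blinded, and drop the surgeon from the list.

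Cost: items 1 and 4 are wording. Under the first route in item 2, women wait up to two years longer to learn their arm. As recruitment began in August 2016 under ethics approval, a protocol amendment with updated participant information may be needed. The second route avoids the wait but gives up the claim of blinded patient-reported results beyond 12 months. Item 3 may require a second assessor at a single center.
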